## **STUDY DESIGN**

This is a multicentre, randomized integrated disease management program to compare the effects of structured care using the JADE portal versus usual care using the DIAMOND portal on incidence of all diabetes-related clinical endpoints in a naturalistic setting.

Ethical approval will be obtained from the local institutional board before commencement of the study. The doctor will explain to eligible patients the rationale for undergoing regular CA to detect silent risk factors and complications and the need to assess the cost-effectiveness of using a team to deliver structured care and empower self-management. With written informed consent and after randomization, a trained nurse will perform the CA using structured protocols in all patients at baseline, 12 and 24 months, further assisted by the doctor and HCA. All patients will be asked to complete simple questionnaires to assess psychological health, quality of life and behaviour during CA visit. The trained nurse will perform simple procedures (e.g. measurement of anthropometric indexes, visual acuity, blood pressure (BP), blood drawing and collecting urine samples).

Apart from assisting the nurse, the HCA will be responsible for entering data, managing the database and maintaining an appointment and filing system. The doctor will focus on taking medical history to diagnose, identify needs and monitor clinical progress. The doctor will also perform eye and feet, and any other relevant, examinations or refer patients to appropriate personnel to undergo these assessments during the CA. All data will be first captured using case report form (CRF) during CA and FU visits followed by data entry. Patients randomized to the JADE group will be followed up 2-4 monthly by a doctor-nurse-HCA team using predefined protocol in group review clinics in order to facilitate group education and promote peer interactions. We expect a doctor-nurse-HCA team to screen 4-6 patients daily and recruit 600 patients within 6-8 months from each centre, giving a total FU period of 2.5-3 years.

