## **SETTING AND PATIENTS**

In this program, 600 consecutive type 2 diabetic patients will be recruited from each participating centre during a 6-8 month period, with randomization to either the JADE or DIAMOND group in a 1:1 ratio.

*Inclusion criteria*

- 1) Type 2 diabetic patients who are willing or can be persuaded to return for 'regular' follow-up at 3-4 monthly intervals
- 2) Aged  $\geq 18$  years
- 3) Patients with newly diagnosed or established disease, treated with lifestyle modification or blood glucose lowering drugs including oral agents with or without insulin
- 4) For newly diagnosed type 2 diabetic patients, their plasma glucose levels should be:
  - a) Fasting plasma glucose (PG)  $\geq 7.0$  mmol/L on 2 or more occasions, and/or
  - b) Random or 2-hour PG  $\geq 11.1$  mmol/L (after 75 gram oral glucose tolerance test) on 2 or more occasions, and/or
  - c) HbA1c  $\geq 6.5\%$

*Exclusion criteria*

- 1) Type 1 diabetes defined as a history of ketosis at diagnosis [acute symptoms with heavy ketonuria ( $>3+$ ) or ketoacidosis] or continuous requirement of insulin within one year of diagnosis (38).
- 2) Patients with reduced life expectancy (e.g. less than 6 months) due to recent diagnosis of advanced cancers (e.g. within last 2 years) and other life-threatening conditions.
- 3) Patients with a mental condition rendering them unable to understand the nature, scope, and possible consequences of the study.
- 4) Patients actively enrolled in another intervention study.
- 5) Patients who are unwilling to return for regular follow up.

**OUTCOME MEASURES***Composite primary endpoint (CRF (1-5))*

- 1) Incidence of all diabetes-related endpoints including:
  - a) cardiovascular events (acute myocardial infarction, revascularisation procedures, heart failure, unstable angina, arrhythmia, stroke, transient ischemic attacks requiring hospital admissions) and related death
  - b) chronic kidney disease (eGFR  $< 60$  ml/min/1.73m^2) or end stage renal disease (dialysis and/or eGFR  $< 15$  ml/min/1.73m^2) and related death
  - c) visual impairment (corrected visual acuity of 20/200 or worse) or eye surgery (cataract removal, retinal surgery and vitrectomy)

- d) lower extremity amputation or foot ulcers requiring hospitalizations
- e) major infections – pulmonary and non-pulmonary requiring hospitalizations
- f) all-site cancers
- g) death

Composite secondary endpoint

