- 11) At baseline, year 1 and 2 as well as close out of study, all outcome measures and medications will be ascertained by phone or face to face interview (CRF: 1-5).

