### Intervention – JADE Group

In the JADE group, the patients are managed by a team of doctor, nurse and HCA, who share different tasks ranging from clinical diagnosis, education, data management and treatment to targets in order to improve the logistics in delivering this complex care protocol, augmented by information technology.

[figure not shown]

- 1) Patients randomized to the JADE group will be followed according to the protocol based on their risk levels. In addition to the CA visit, all subsequent FU visits will be documented followed by data entry into the JADE portal with issue of reports to both patients and doctor to promote sharing of information and informed decisions.

| Risk stratification                           | Very-high risk
4                                                 | High risk
3 | Medium risk
2 | Low risk
1 |
|-----------------------------------------------|---------------------------------------------------------------------|----------------|------------------|---------------|
| Cardiovascular renal complication             | ≥ 1                                                                 | 0              | 0                | 0             |
| Any risk score                                | NA                                                                  | ≥ SP           | ≥ ST and < SP    | < ST          |
| Stratification parameters                     | NA                                                                  | ≥ 3            | 2                | 0-1           |
| eGFR                                          | NA                                                                  | < 60           | 60-90            | ≥ 90          |
| Recommended number of medical visits per year | 6 or more                                                           | 4 or more      | 3 or more        | At least 2    |
| Comprehensive assessment                      | Every 12-18 months                                                  |                |                  |               |
| Other recommendations                         | Counselling/laboratory tests/telephone calls between medical visits |                |                  |               |

Parameters for risk stratification:

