- 3) If not yet put in place, the nurse/HCA will prepare a clinic folder for each patient and create a system to facilitate appointment booking and tracking of default.
- 4) Patients are booked for reviews led by the doctor-nurse-HCA team every 2-4 months, preferably in a setting different from the busy clinics in order to facilitate group education and promote peer support.
- 5) Between each FU visit, the nurse or HCA will contact the patient by phone or email to remind them of the appointments (e.g. medical FU visit or laboratory tests), adhere to medications and healthy lifestyles, perform self glucose monitoring and provide psychosocial support, as appropriate.
- 6) Before each FU visit, the nurse will ensure all tests (e.g. HbA1c, lipids, blood haemoglobin, renal function etc) ordered by the doctor are available in the folder for decision making.
- 7) At each FU visit, the patients will first see the nurse for record of BP, body weight and blood glucose (or HbA1c) as appropriate and enter them in the CRF. Patient's compliance will also be checked at each visit.
- 8) After the FU visit, the patients will see the nurse to clarify any issues and concerns. The nurse will reinforce compliance and record any changes in medications and note any procedures or tests ordered by the doctor. As and when appropriate, the nurse will remind doctors on action items prompted by the JADE e-portal, if omitted.
- 9) After each FU visit, the nurse will issue summary reports to be given to patients and doctors to promote sharing of information.

10) The FU and CA reports can be given to the patient on the same day of the visit or emailed or sent by post to patient as appropriate.

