#### Intervention - DIAMOND group

Patients randomized to the DIAMOND group will receive usual care after the initial CA with repeat CA at 12 and 24 months.

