## **DEFAULT AND MISSING DATA**

This is a translational research which aims to evaluate the effectiveness of team-based, protocol-augmented care on clinical endpoints in a naturalistic environment. No new investigational drugs will be used and all care processes are recommended by international guidelines. Given the diversity of health care systems in these countries, investigators will be asked to first define the processes of ‘usual care’ in their clinics. We shall also assess the needs and feasibility of implementing team-based protocol driven care in their clinic setting (see appendix). To reduce the number of defaulters in the JADE and DIAMOND groups, the doctor and nurse will explain clearly the nature of the program and seek their consent for contacts via phone or email or letter regarding clinical status, notably death or major clinical events or hospitalizations at least once yearly even if they are not able to return for repeat CA.

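### JADE patients are seen every 2-4 months and DIAMOND patients only yearly under the protocol; nothing confines primary events to sources common to both arms, so forgettable DIAMOND events may be under-counted

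*Protocol*

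**What the plan says.** **Contact in JADE.** Study Design: "Patients randomized to the JADE group will be followed up 2-4 monthly by a doctor-nurse-HCA team". Intervention – JADE Group, item 1: "all subsequent FU visits will be documented followed by data entry into the JADE portal". Item 5 of that section: "Between each FU visit, the nurse or HCA will contact the patient by phone or email".

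**Contact in DIAMOND.** Intervention – DIAMOND Group: patients "will receive usual care after the initial CA with repeat CA at 12 and 24 months". The executive summary says that this arm has no predefined FU schedule. Default and Missing Data leaves each site to define its own usual care.

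**Data capture.** Study Design: "All data will be first captured using case report form (CRF) during CA and FU visits followed by data entry". Comprehensive Assessment, item 11, covers baseline, years 1 and 2 and close-out for all patients: "all outcome measures and medications will be ascertained by phone or face to face interview", on CRF 1-5. Outcome Measures ties the composite primary endpoint to those same forms. Comprehensive Assessment, item 1(f), also asks every patient about major clinical events and hospitalizations.

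**Safeguards.** Patients who do not return are to be contacted "at least once yearly even if they are not able to return for repeat CA". Enrolment, item 2, obtains consent to collect clinical data at least yearly for 3 years. An adjudication committee reviews narratives and supporting documents.

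**Endpoint wording.** Primary endpoint item (a) is a list of cardiovascular events that ends with "transient ischemic attacks requiring hospital admissions".

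**The concern.** The arms share the dates on which outcomes are ascertained, but not the information available on those dates. The staff who complete CRF 1-5 for a JADE patient have met that patient several times in the year and spoken to them in between. For a DIAMOND patient, protocol contact since the last ascertainment may be nil, and the interview, possibly by phone, may rest on about 12 months' recall.

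The components are not equally exposed. Deaths, dialysis and amputations are unlikely to be lost. Admissions for infection, foot ulcer or TIA, and episodes of heart failure, unstable angina or arrhythmia, are easier to forget or misdate. In item (a) it is also unclear whether the hospital-admission condition reaches beyond TIA. If it does not, an outpatient diagnosis of heart failure, unstable angina or arrhythmia made at an extra JADE review counts as a primary event.

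Any such loss falls on the control arm and works against the trial's own hypothesis. An event that was never recorded cannot be recovered at analysis. How often eGFR is measured in each arm is a separate matter and is not part of this point.

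**Working it through.** **Step 1. Do the arms have the same route to an event?**

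| | JADE | DIAMOND |
|---|---|---|
| CRF 1-5 interview at year 1, year 2, close-out | yes | yes |
| Event history at CA | yes | yes |
| Protocol review every 2-4 months, entered in the portal | yes | no |
| Calls or emails between reviews | yes | no |
| Required search of hospital records | no | no |
| Rule limiting primary events to common sources | none stated | none stated |

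The first two rows are equal. The next two are not, and the last two show that nothing in the protocol neutralises the difference.

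**Step 2. Reproduce the plan's figure.** Inputs from Sample Size Calculation and Data Analysis: 2-year risk 0.10 (usual care) and 0.08 (structured care), two-sided alpha 0.05, 80% power, 1:1 allocation.

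n = [1.96·√(2p̄(1−p̄)) + 0.842·√(p₁(1−p₁) + p₂(1−p₂))]² / (p₁−p₂)², with p̄ = 0.09, gives 3213 per arm. The continuity correction, (n/4)·[1 + √(1 + 4/(n·|p₁−p₂|))]², gives 3313, the plan's value before its attrition allowance.

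**Step 3. Power under incomplete capture.** Multiply each arm's true risk by the share of events captured, then

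power = Φ{ [ |p₁−p₂|·√n − 1.96·√(2p̄(1−p̄)) ] / √(p₁(1−p₁) + p₂(1−p₂)) }, n = 3313.

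With complete capture: (0.02·√3313 − 1.96·0.4047)/0.4045 = 0.885, power 81%. This exceeds 80% because the formula carries no continuity correction. With 10% of DIAMOND events missed, p₁ = 0.09: (0.01·√3313 − 1.96·0.3944)/0.3943 = −0.50, power 31%.

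The protocol gives no capture rate, so every missed share below is an assumption.

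| DIAMOND missed | JADE missed | Observed risks | Ratio | Power |
|---|---|---|---|---|
| 0% | 0% | 10.0% v 8.0% | 0.80 | 81% |
| 5% | 0% | 9.5% v 8.0% | 0.84 | 58% |
| 10% | 0% | 9.0% v 8.0% | 0.89 | 31% |
| 20% | 0% | 8.0% v 8.0% | 1.00 | effect gone |
| 10% | 5% | 9.0% v 7.6% | 0.84 | 54% |
| 10% | 10% | 9.0% v 7.2% | 0.80 | 77% |

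If only half of the events are of a forgettable kind and 10% of those are missed, the overall loss is 0.5 × 10% = 5%, which is the second row.

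The plan's 6% v 4.8% case (5734 per arm) and 4% v 3.2% case (8760 per arm) give the same powers for one-sided losses of 5% and 10%: 58% and 31%.

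**Step 4. No true effect.** With both true risks at 10% and 10% of DIAMOND events missed, the observed risks are 9% and 10%. The ratio is 0.10/0.09 = 1.11, and the chance of a significant result against JADE is about 28%.

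The last row of the table shows that equal loss does little harm. The damage comes from the difference between the arms.

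**The case against.** The case against has real weight.

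- **Common forms and dates.** CRF 1-5 are completed at the same times in both arms, and events are also asked about at each CA. A reader might infer that an interview is the only planned source for DIAMOND. It is not: history is taken at CA, clinical data may be obtained under the consent, and reported events need supporting documents. But these are yearly questions, a permission, and a review of events already reported. None requires a search for unreported ones.
- **What JADE visits record.** A reader might infer that the team holds a dated record of every interim admission. The JADE intervention section lists blood pressure, weight, glucose or HbA1c, compliance, medication changes and tests ordered. Admissions are not named. It remains likely that an admission surfaces at such a review, and nothing keeps that knowledge off CRF 1-5.
- **DIAMOND patients are not unseen.** They receive usual care, and inclusion criterion 1 requires willingness to return every 3-4 months. Twelve months' recall is therefore the worst case. How far usual care shortens it depends on the site, and no event capture at those visits is specified.
- **Unseen material.** CRF 1-5 are not shown and may already go through the endpoints one by one. That would help the interview, but would not equalise what the interviewer already knows.
- **Illustrative numbers.** Complete JADE capture is the most unfavourable contrast. A patient with one forgotten admission may also still count through another component.

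**Conclusion.** The point holds as a risk left uncontrolled. Contact is unequal by design, and the protocol neither requires an arm-neutral search for events nor excludes events learned only through JADE contacts from the primary endpoint. DIAMOND events may be under-counted. A reader might go further and conclude that they are under-counted, but the documents do not support that: they give no capture rate, and formal ascertainment follows one schedule in both arms.

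If there is a differential, it biases the ratio towards or above 1. At the plan's 10% v 8% with 3313 per arm, a one-sided loss of 5-10% would cut power from 81% to between 58% and 31%. A 10% loss in both arms would leave it at 77% with the ratio intact. These figures rest on assumed missed shares, complete JADE capture in the one-sided rows, loss counted per patient with an event, and a normal approximation. They show sensitivity and do not estimate the actual bias.

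**What to change.** 1. **Comprehensive Assessment, item 11.** Require CRF 1-5 at month 12, month 24 and close-out to be completed in both arms from the same two sources: (i) an interview that asks about each endpoint in turn for the time since the last ascertainment, and (ii) a check, for the same window, of hospital admission or discharge records available to the site, under the consent in Enrolment, item 2. State that JADE FU notes, call logs and the JADE clinic folder are not used for this. Otherwise the record check would bring the asymmetry back.
2. **Data Analysis.** Count events found by these two sources in the primary analysis. Add events known only from JADE FU contacts in a sensitivity analysis.
3. **Outcome Measures, primary endpoint item (a).** State that the hospital-admission condition applies to heart failure, unstable angina and arrhythmia as well as TIA, so that outpatient diagnoses at extra JADE reviews do not count.

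The cost is revised CRF wording and some local record checking at three time points. Consent and supporting documents for adjudication are already planned. The downside is that a few genuine JADE events, known only from FU contacts, leave the primary count; the sensitivity analysis shows how much they matter.

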## **SETTING AND PATIENTS**

In this program, 600 consecutive type 2 diabetic patients will be recruited from each participating centre during a 6-8 month period, with randomization to either the JADE or DIAMOND group in a 1:1 ratio.

*Inclusion criteria*

- 1) Type 2 diabetic patients who are willing or can be persuaded to return for 'regular' follow-up at 3-4 monthly intervals
- 2) Aged  $\geq 18$  years
- 3) Patients with newly diagnosed or established disease, treated with lifestyle modification or blood glucose lowering drugs including oral agents with or without insulin
- 4) For newly diagnosed type 2 diabetic patients, their plasma glucose levels should be:
  - a) Fasting plasma glucose (PG)  $\geq 7.0$  mmol/L on 2 or more occasions, and/or
  - b) Random or 2-hour PG  $\geq 11.1$  mmol/L (after 75 gram oral glucose tolerance test) on 2 or more occasions, and/or
  - c) HbA1c  $\geq 6.5\%$

*Exclusion criteria*

- 1) Type 1 diabetes defined as a history of ketosis at diagnosis [acute symptoms with heavy ketonuria ( $>3+$ ) or ketoacidosis] or continuous requirement of insulin within one year of diagnosis (38).
- 2) Patients with reduced life expectancy (e.g. less than 6 months) due to recent diagnosis of advanced cancers (e.g. within last 2 years) and other life-threatening conditions.
- 3) Patients with a mental condition rendering them unable to understand the nature, scope, and possible consequences of the study.
- 4) Patients actively enrolled in another intervention study.
- 5) Patients who are unwilling to return for regular follow up.

**OUTCOME MEASURES***Composite primary endpoint (CRF (1-5))*

- 1) Incidence of all diabetes-related endpoints including:
  - a) cardiovascular events (acute myocardial infarction, revascularisation procedures, heart failure, unstable angina, arrhythmia, stroke, transient ischemic attacks requiring hospital admissions) and related death
  - b) chronic kidney disease (eGFR  $< 60$  ml/min/1.73m^2) or end stage renal disease (dialysis and/or eGFR  $< 15$  ml/min/1.73m^2) and related death
  - c) visual impairment (corrected visual acuity of 20/200 or worse) or eye surgery (cataract removal, retinal surgery and vitrectomy)

- d) lower extremity amputation or foot ulcers requiring hospitalizations
- e) major infections – pulmonary and non-pulmonary requiring hospitalizations
- f) all-site cancers
- g) death

Composite secondary endpoint

2) Proportions of patients with improved control of risk factors defined as:

- a) 2 or more of the ‘ABC’ targets:
  - i) HbA1c < 7%
  - ii) BP < 130/80 mmHg
  - iii) LDL-C < 2.6 mmol/L
- b) and/or
- c) 2 of the following changes in risk factor control:
  - i) at least 0.5% reduction in HbA1c
  - ii) at least 5 mmHg reduction in systolic BP
  - iii) at least 0.5 mmol/L reduction in LDL-C
  - iv) at least 3% reduction in body weight

Composite tertiary endpoint

- 3) Quality of life (ED-5Q)
- 4) Frequency of hypoglycaemia (in the last 3 months) as recorded in the JADE CA form
- 5) Behavioral changes in last 3 months as recorded in the JADE CA form
  - a) Frequency of Self Blood Glucose Monitoring
  - b) Adherence to balanced eating
  - c) Adherence to regular exercise
- 6) CQ4 for compliance
- 7) PHQ-9 for depression
- 8) Hospitalization days and cost-effectiveness analysis
- 9) Additional questionnaires are available for interested investigators to assess other psychological parameters (self efficacy, diabetes related stress, perception of happiness, personal habits) and self-care activities to explore reasons which may explain differences in outcomes between the 2 groups (see appendix).

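### The eGFR below 60 component of the primary endpoint is not tied to measurements common to both arms, so CKD can be detected more often or earlier in JADE without any true difference

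*Protocol*

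**What the plan says.** **Endpoint.** Protocol, Outcome Measures, composite primary endpoint, item (b) lists "chronic kidney disease (eGFR" below 60 ml/min/1.73m²) beside end-stage renal disease (dialysis and/or eGFR below 15) and related death. The composite is an incidence. The item does not state which visits supply the eGFR, whether a low value must be confirmed, or how a patient already below 60 at baseline is handled. Such patients are eligible: eGFR below 60 is one criterion for the high-risk level in the risk stratification, and no exclusion criterion removes them.

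**JADE.** Under Intervention – JADE Group: "Patients are booked for reviews led by the doctor-nurse-HCA team every 2-4 months". The risk table in that section recommends between at least 2 (low risk) and 6 or more (very high risk) medical visits a year, and names laboratory tests between visits among its other recommendations. Before each visit the nurse checks that tests (the examples include "blood haemoglobin, renal function etc) ordered by the doctor are available in the folder for decision making"). On data capture: "In addition to the CA visit, all subsequent FU visits will be documented followed by data entry into the JADE portal".

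**DIAMOND.** These patients "will receive usual care after the initial CA with repeat CA at 12 and 24 months". The executive summary adds that this arm has no predefined follow-up schedule between assessments.

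**Common to both arms.** The Comprehensive assessment (CA) section includes eGFR for all patients at baseline, 12 and 24 months. It also has all outcome measures ascertained by phone or face-to-face interview at baseline, years 1 and 2 and close-out. An adjudication committee reviews pre-defined clinical events (Site Visits and Event Adjudication).

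**The concern.** An eGFR threshold event exists only if blood is drawn and the result reaches the study. eGFR varies within a person, so more measurements give more chances of one value below 60, and an earlier first one. Both the opportunity for interim testing and the routine capture of its results are greater in JADE than in DIAMOND.

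If interim values count, the arms are compared on unequal numbers of looks at the same threshold. The bias runs against JADE: it can hide a real benefit or, if CKD is a large part of the composite, suggest harm. The earlier dating of JADE events would also carry into the planned Kaplan-Meier comparison.

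The matter is likely to touch many patients. The sample size section reports that most patients in the first-year JADE data were at high or very high risk, the levels for which 4 or more and 6 or more visits a year are recommended.

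**Working it through.** **1. The plan's own reference figure.** The protocol gives no CKD rate and no eGFR distribution. Its sample size table gives 3313 per group for 2-year proportions 0.10 and 0.08 (HR 0.8, 80% power, alpha 0.05).

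- Uncorrected: n = [1.96·√(2·0.09·0.91) + 0.842·√(0.10·0.90 + 0.08·0.92)]² / 0.02² = 3213.
- With continuity correction: n′ = (n/4)·[1 + √(1 + 4/(n·0.02))]² = 3313, which matches the table.

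**2. Detection ratio with no treatment effect.** Both arms were simulated with identical eGFR trajectories, 200,000 patients per scenario. Every eGFR input is an assumption:

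- mean 80-90, between-patient SD 20;
- slope −2 per year (SD 2);
- within-patient SD 3-7.

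An event is any single post-baseline value below 60 within 24 months, among patients with measured baseline of at least 60. DIAMOND is tested at months 12 and 24 only. The last column is the scenario with mean 90 and within-patient SD 5.

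| Testing schedule | 2-year CKD, all scenarios | Ratio to months 12 and 24 only | Mean 90, within-SD 5 |
|---|---|---|---|
| Months 12 and 24 | 4.9-14.0% | 1.00 | 6.2% |
| 6-monthly | 5.6-18.2% | 1.16-1.33 | 7.8% |
| 4-monthly | 6.2-21.0% | 1.27-1.55 | 8.9% |
| 3-monthly | 6.6-23.0% | 1.35-1.70 | 9.7% |
| 2-monthly | 7.3-25.8% | 1.46-1.96 | 10.8% |

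If interim JADE values do not count, or if DIAMOND is tested and captured equally often, the ratio is 1.00 by construction. Intermediate practice (renal tests at only some JADE visits, or some interim testing in DIAMOND) falls between 1.00 and the row concerned.

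**3. Carry-over to the composite.** Let s be the share of DIAMOND composite events that are CKD, and R the ratio above. To a first approximation, observed ratio = true ratio × [1 + s·(R − 1)]. The share s is not in the protocol. With a true ratio of 0.80:

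- s = 0.25, R = 1.2: 0.80 × 1.05 = 0.84
- s = 0.50, R = 1.2: 0.80 × 1.10 = 0.88
- s = 0.50, R = 1.35: 0.80 × 1.175 = 0.94
- cancelled completely when s·(R − 1) = 0.25, for example s = 0.50 and R = 1.5
- R = 1.00: 0.80 for any s

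**4. Effect on power.** Take 3313 per group and 10% in usual care. Power ≈ Φ(d/SE − 1.96), where d is the difference in proportions and SE = √[(p₁q₁ + p₂q₂)/3313].

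- 0.80: d = 0.020, SE = 0.00703, power about 81%
- 0.88: d = 0.012, SE = 0.00717, power about 39%
- 0.94: d = 0.006, SE = 0.00727, power about 13%

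**The case against.** **Testing is not prescribed.** It is tempting to read the protocol as testing renal function every 2-4 months in JADE. It does not say so. The reviews are 2-4 monthly; renal function is one example among tests the doctor may order. What the nurse records at each visit is blood pressure, weight and glucose or HbA1c. This stands.

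**DIAMOND is not necessarily untested.** Inclusion criterion 1 asks patients in both arms to accept follow-up at 3-4 monthly intervals, and each site defines its own usual care, which may include renal tests. This also stands, so a reader may not infer that JADE will show more CKD events, only that it can. Capture still differs: JADE follow-up visits go into the portal, while no routine entry of interim DIAMOND results is described.

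**There is a common capture route.** The primary endpoint heading refers to CRF 1-5, and those forms are completed at the same times in both arms; adjudication follows. This aligns when outcomes are asked about. It does not say whether an interim eGFR known at that time counts, and neither an interview nor a committee can recover a value that was never drawn.

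**The detail may sit elsewhere.** Derivation rules often belong to an analysis plan or adjudication charter, neither of which is shown. The word incidence already implies that prevalent CKD is not a new event. That limits the weight of the baseline point. The source of the measurement is different: it decides whether the primary endpoint is ascertained alike in both arms, and the schedule as written makes that doubtful.

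**The size is assumed.** Correct. No eGFR input and no CKD share comes from the protocol, and 1.00 belongs in the range.

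**Conclusion.** The point holds as an open route to arm-dependent detection bias, not as a demonstrated bias. The primary composite includes a laboratory threshold that is not restricted to common visits. Scheduled contact and data capture are greater in JADE, and no passage excludes interim values. The direction, if it occurs, is against the intervention.

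The null CKD ratio runs from 1.00, through about 1.2-1.3 (JADE tested 6-monthly, DIAMOND not tested between assessments), to about 2.0 (JADE 2-monthly). These figures rest on the assumed eGFR distributions and on interim values counting. The composite is affected in proportion to a CKD share that the protocol does not give; at a share of one half, even a ratio of 1.2 would move a true 0.80 to 0.88.

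A reader might infer that the planned HR of 0.8 will be cancelled. The documents do not support that: it needs s·(R − 1) to reach 0.25, and neither quantity is fixed. Should fix, with moderate confidence.

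**What to change.** Reword item (b) of the primary endpoint as follows:

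- In both arms, take eGFR-based events only from the 12- and 24-month comprehensive assessments.
- Count incident CKD (below 60) only in patients whose baseline assessment eGFR is at least 60. Patients below 60 at baseline contribute renal events through the existing end-stage criterion.
- Count dialysis and renal death whenever they occur.
- Do not use eGFRs from interim JADE follow-up visits for the endpoint.

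This equalises the scheduled looks. Requiring confirmation alone would not: in the mean 90, within-SD 5 scenario, two consecutive scheduled values below 60 occur in 2.1% with annual testing and 4.5% with 3-monthly testing.

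The cost is endpoint wording only, since eGFR is already measured at these assessments in both arms; no visit, test or care process changes. Interim crossings go unused, and events are dated to the yearly assessment. Patients followed only by phone have no assessment eGFR, so unequal attendance could still unbalance detection; attendance at the 12- and 24-month assessments should be reported by arm.
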